## 2. Methods/Design

### 2.1. Study Design

This study is a randomized, double-blind, placebo-controlled, phase II trial to evaluate the efficacy and safety of BJIGT for PAR. The trial will be conducted at the Daejeon University Daejeon Korean Medicine Hospital in Korea. We followed the methods of Lee et al. [25].

A total of 105 participants will be recruited for this trial and randomly assigned to a high-dose BJIGT group, standard-dose BJIGT group, or control group (placebo) in a 1 : 1 : 1 allocation ratio. The trial will consist of a 1-week run-in period after screening and a 4-week treatment period. Participants will take medications three times a day for 4 weeks, with visits at 2-week intervals; the detailed study design is summarized in Figure 1 and Table 1.

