
To determine whether the rhinitis is allergic, potential participants will be examined using MAST at the screening, and participants classified as class 2 or higher in the MAST that tests 108 types of allergens will be enrolled. Each patient's enrollment will be determined by the investigator, a Korean medicine doctor who treats allergies and respiratory diseases. During the trial period, the participant can voluntarily withdraw at any time or can be dropped at the discretion of the researcher.

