#### 2.2.2. Sample Size

The number of subjects is evaluated on the basis of detecting significant differences in the primary outcome, mean change of TNSS before and after medication among the groups with AR patients. In an earlier clinical study that evaluated other herbal medicines compared with placebo, the difference in TNSS was reported to be 0.97 with a standard deviation of 1.3 [14]. With a power of 80% (1–*β*) and a significance level of 5% (*α*), the target sample size is 29 patients per group. Considering an assumed dropout rate of 20%, a total of 105 subjects (35 subjects per group) will be required. Similarly, the number of subjects in previous exploratory phase II trials ranged from 20 to 42 per group [26–28].

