#### 2.4.3. Safety Assessment

Safety will be assessed through laboratory examinations, vital signs, and adverse events (AEs). To observe the safety of the participants, complete blood cell counts, blood coagulation test, blood chemistry examination (liver and kidney function test), serum hepatitis test, and urine test will be conducted at screening and at the fourth and fifth visits. The investigator will check vital signs and any unexpected or expected AEs at every visit and record details on a case report form (CRF). If serious AEs occur, the investigator will promptly stop the subject from taking medication and report it in accordance with the guidelines of the IRB.

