### 2.7. Statistical Analysis

An independent statistician will analyze the data using SAS Analytics Pro. A full analysis set (FAS) is defined as the analysis based on intention-to-treat (ITT) principles, including the subjects who received at least one trial intervention when evaluating effectiveness. In this trial, efficacy evaluation will be primarily based on ITT analysis, and per-protocol (PP) analysis will be applied as a secondary analysis, including the subjects completing the entire trial without violating the protocol.

The demographic characteristics and baseline data will be expressed as means and standard deviations (SD) for continuous variables, and frequencies and percentages for categorical variables. The baseline differences between groups will be compared using an independent *t*-test for continuous values and the *χ*^2^ test or Fisher's exact test for categorical values. The efficacy outcome measures and the mean differences of TNSS from baseline to the treatment period will be analyzed by analysis of covariance (ANCOVA) with baseline data as a covariate for linear mixed models (LMMs). The baseline data are defined as the mean TNSS per day in the run-in period and will be compared with the diary-based mean TNSS for the 2-week treatment period or 4-week treatment period. The efficacy analysis methods are the same for TNSS by PI and Sasang constitution, KARQLQ, and biomarkers. The overall assessment of AR after the trial will be analyzed using a general linear model. All analyses will be set at a 5% significance level.

Safety evaluation will be conducted in the subjects who took one or more interventions, and the investigator will confirm at least one safety-related data set by visit or call after the intervention. A comparison of the number of AEs related with the trial will be conducted using the Kruskal–Wallis test, and group comparisons of the proportion of subjects who experienced one or more AEs will be analyzed using Pearson's *χ*^2^ or Fisher's exact test.

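### The test of AE numbers is worded to count only trial-related events and ignores observation time, so it drops recorded events and could understate an excess if early stopping differs by arm

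*Protocol article*

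**What the plan says.** The protocol article names two between-group AE comparisons, both in one sentence of section 2.7.

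- Event numbers: "A comparison of the number of AEs related with the trial will be conducted using the Kruskal–Wallis test".
- Subjects affected: "group comparisons of the proportion of subjects who experienced one or more AEs will be analyzed using Pearson's" chi-square or Fisher's exact test. This half does not repeat the limit to trial-related events.

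Four other statements bear on the point.

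- Population (section 2.7): "Safety evaluation will be conducted in the subjects who took one or more interventions", with at least one safety record confirmed by visit or call after the intervention.
- Collection (section 2.4.3): "The investigator will check vital signs and any unexpected or expected AEs at every visit and record details on a case report form". Collection is not limited by causality.
- Early stopping: "If serious AEs occur, the investigator will promptly stop the subject from taking medication" (section 2.4.3), and "the participant can voluntarily withdraw at any time or can be dropped at the discretion of the researcher" (section 2.2.1). Section 2.2.2 allows for 20% dropout overall, with no split by arm.
- Planned duration (section 2.1): "The trial will consist of a 1-week run-in period after screening and a 4-week treatment period". It is the same in all arms.

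**The concern.** There are two separate weaknesses in the count test.

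**Which events are counted.** All AEs are collected, but on a plain reading only those judged related to the trial enter the test of numbers. Random allocation and blinding already make the comparison of all events fair. A relatedness filter adds judgement and removes events from a small data set. It also leaves the two halves of one sentence working on different event sets, with no reason given.

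**How long each person is observed.** The Kruskal–Wallis test ranks raw counts per subject. A subject observed for a few days is ranked against one observed for four weeks as if both had the same opportunity to report events. Since AEs can themselves lead to stopping, observation time may depend on tolerability.

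Safety and the choice of a suitable dose are both stated aims of the trial (end of section 1), so the AE contrast between each dose and placebo matters. A diluted contrast would make a less well tolerated dose look closer to placebo than it is.

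**Working it through.** The article gives no figure for the AE comparison, so there is none to reproduce. The arm size used below is its own: 29 × 1.2 = 34.8, rounded up to 35 per arm and 3 × 35 = 105 in total. AE rates, rate ratios and dropout by arm are not in the article. Every such value below is an assumption. The four-week period follows the text. Table 1 labels visits 4 and 5 as weeks 4 and 8, which has to be reconciled with the text, but the first calculation depends only on fractions of the period.

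**1. Dilution of the count ratio.** Suppose recording ends at stopping and events accrue at a constant rate. With dropout d, and dropouts observed for a fraction f of the period, mean exposure is 1 − d(1 − f). The apparent ratio is the true ratio times the ratio of exposures. Take a true ratio of 1.5, with d = 0.30 on high dose and 0.10 on placebo:

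- f = 0.50: exposures 0.85 and 0.95; 1.5 × 0.85/0.95 = 1.34.
- f = 0.15: exposures 0.745 and 0.915; 1.5 × 0.745/0.915 = 1.22.
- Equal d and f in both arms: the exposures cancel and the ratio stays 1.5.

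**2. When would the order reverse?** Suppose only one arm stops early, with a share d stopping at week t of 4. Its mean count is multiplied by 1 − d(1 − t/4), and it shows fewer events only if its true ratio is below the inverse of that factor.

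| Share stopping, week | Factor | Reversal only if true ratio is below |
|---|---|---|
| 20%, week 2 | 0.90 | 1.11 |
| 20%, week 1 | 0.85 | 1.18 |
| 40%, week 2 | 0.80 | 1.25 |
| 40%, week 1 | 0.70 | 1.43 |

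At a true ratio of 2 the apparent ratio is still 1.4 to 1.8.

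**3. Effect on the Kruskal–Wallis test.** This was simulated with Poisson counts, 35 per arm and 4,000 runs per scenario. With 0.6 AEs per subject per four weeks in two arms and a true ratio of 1.5 in the third:

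- Full exposure: power 27%, mean count 0.90 against 0.60.
- 20% of that arm stop at week 1: power 9%, mean count 0.76.
- 40% stop at week 1: power 5%, mean count 0.63, still above 0.60.
- 20% stop at week 1 in all arms: power 23%, with the ratio of mean counts still about 1.5.

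With no true difference and 40% of one arm stopping at week 1, rejection rises from about 5% to between 10% and 29% for base rates of 0.3 to 1.0, and that arm looks safer. With 20% stopping in all arms it stays at about 5%.

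**4. Cost of the relatedness filter.** Suppose the blinded judgement keeps half of the events in every arm. The base rate then falls from 0.6 to 0.3. At full exposure, power falls from 27% to 15% for a ratio of 1.5, and from 74% to 44% for a ratio of 2. If the judgement were accurate and removed mainly background events, the loss would be smaller or could become a gain; the article gives nothing on which to judge that.

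**The case against.** A reader might infer that an arm that drives people off treatment will show fewer AEs. The documents do not support that. Steps 1 and 2 of the working show dilution, and reversal needs a modest true ratio together with strongly unequal stopping.

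Further points on the other side, and what stands of each:

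- **The second comparison catches AE-driven stoppers.** The safety set keeps anyone who took at least one intervention and has a safety record, so a person who leaves because of an AE counts as affected however short the exposure. This stands. The comparison does not repair the count test, because it ignores repeat events and observation time too.
- **Step 1 overstates the loss for AE-driven leavers.** With a rate of 0.9 on high dose, a person leaving at 15% of the period is credited with 0.9 × 0.15 = 0.135 events, yet someone who left because of an AE has at least one. As a rough check, give each leaver one event and each stayer the average. High dose is then 0.7 × 0.9 + 0.3 × 1 = 0.93, placebo is 0.9 × 0.6 + 0.1 × 1 = 0.64, and the ratio is 1.45. Most of the dilution disappears, provided that the event is counted as related. This stands.
- **Recording may continue after stopping.** The article stops medication after a serious AE; it does not say that AE recording stops, and safety data may be obtained by call. This stands, so the shortened window is an inference.
- **The wording may be loose English** for events arising in the trial, and no causality assessment is described. That is possible. The sentence then needs clarifying rather than correcting. If causality is judged, it is judged blind, so it loses information without by itself favouring an arm.
- **Exposure-adjusted rates are commonly left to an analysis plan.** True, and their absence is not the point. The point is that the article fixes the event set of the count test, and fixes it narrowly.

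**Conclusion.** The point holds in a modest form. As worded, the test of AE numbers is restricted to trial-related events although all AEs are collected, and it does not use the event set of the proportion test beside it. That rests on the text alone, subject to the ambiguity in its English.

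The observation-time weakness is conditional. It needs early stopping that differs by arm and AE recording that ends at stopping. Under the assumed 30% and 10% dropout, a true ratio of 1.5 would read as 1.34 or 1.22, and closer to 1.45 if each leaver contributes the event that made them leave. With equal dropout there is no distortion. The short, equal planned treatment period limits the effect further, so a person-time analysis is a supportive addition and not a necessary replacement.

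**What to change.** In section 2.7, and in the analysis plan if there is one:

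1. Compare the number of all AEs starting after the first randomised dose, whatever the causality judgement. Use the same event set for the proportion of subjects with at least one AE. The start point also settles whether events during the placebo run-in count. The Kruskal–Wallis test can stay.
2. Keep trial-related AEs as a supportive table.
3. As a supportive summary, report events per person-week of observation for each dose against placebo, with observation running from the first randomised dose to the last safety contact. State whether AE recording continues after treatment stops.

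The cost is a change of wording and one extra table. AEs are already recorded on the case report form at every visit. The person-week summary needs the date of the last safety contact, and it assumes a roughly constant AE rate. That assumption is weak if events cluster early, which is another reason to keep the summary supportive.

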Complementary medicine has been broadly used for the treatment of AR [12], and especially in Asian countries, many trials have evaluated the efficacy of several herbal medicines [13, 14], acupuncture [15], and so on. Bojungikgi-tang (BJIGT), also known as Bu-Zhong-Yi-Qi-Tang or Hochu-ekki-to, is an herbal medication that has been widely used in traditional medicine from old times. JIGT means that “tonify the middle and augment qi,” implying strengthening the digestive system and the immune system against many kinds of infections [16] and treating debilitating conditions resulting from chronic diseases [17]. Because of these effects, BJIGT is clinically used for various diseases such as atopic dermatitis, cancer-related fatigue, and anorexia. We paid attention to the anti-inflammatory and immunoregulatory effects of BJIGT for allergic diseases. According to previous studies, in preclinical trials, BJIGT showed inhibitory effects on the increase in the number of eosinophils and protective effects of nasal mucosal tissue in the AR [18] and immune-modulatory effects including downregulating Th2 responses, decreasing IgE, eotaxin, and eosinophils in the allergic asthma model [19]. These effects may be related to the reduction in allergic symptoms. In clinical trials, the nasal symptomatic scores were significantly improved in the BJIGT treatment group and BJIGT suppressed IgE, PGE2, LTC4, and COX-2 mRNA expression in IL-4-stimulated PMN in patients with PAR [20, 21]. Several survey studies have demonstrated that BJIGT was the second most clinically used national health insurance herbal medicine for AR or PAR in Korea [22, 23]. In addition, the safety of BJIGT has been proved in the trial of 13-week oral repeated-dose toxicity [24]. However, no randomized controlled trial has evaluated BJIGT compared with placebo in the treatment of AR in Korea.

We hypothesize that BJIGT would improve nasal symptoms in patients with PAR. The aim of this study is to investigate the efficacy and safety of BJIGT in the treatment of PAR and to determine the suitable dosage of BJIGT. Therefore, we planned a randomized, double-blind, placebo-controlled, phase II trial of two different doses of BJIGT in comparison with placebo.

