## 4. Discussion

AR is a common disease with a high prevalence and significantly affects QOL [3]. AR is usually prolonged, but conventional medications currently used for AR have adverse effects in some patients, especially in long-term use. Antihistamines may cause sedation, fatigue, and impaired mental status and are less effective for nasal congestion [10]. Intranasal corticosteroids have adverse effects, including headache, epistaxis, throat irritation, and nasal dryness, and decongestants are effective for nasal obstruction, but usage for more than one week may induce drug tolerance [35]. Therefore, other additional medicines that can be used long term are required.

BJIGT is a widely known herbal medication in various Asian countries and is used for the treatment of allergic diseases. In previous studies, BJIGT showed anti-inflammatory and immunoregulatory effects by suppressing eosinophils, IgE antibody, cytokines, and histamine related to early-phase response and late-phase response of AR, leading to clinical improvement [18–21, 36]. These effects support that BJIGT may be beneficial for patients with AR.

Although BJIGT is an herbal drug that has already been clinically used for AR, there have been no randomized controlled trials for Korean patients with PAR. This study will support evidence for the efficacy and safety of BJIGT in a standard design and raises objective grounds for Korean medicine used in clinical practice. Further, we expect that BJIGT with a suitable dosage is recommended as a complementary medicine for PAR.

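### The only between-group AE analyses the article names are significance tests at 5%, which were not sized for safety and give no estimate or bound for either dose against placebo

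*Protocol article*

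**What the plan says.** The Introduction makes safety and dose choice aims alongside efficacy: "The aim of this study is to investigate the efficacy and safety of BJIGT in the treatment of PAR and to determine the suitable dosage". The Discussion expects that "This study will support evidence for the efficacy and safety of BJIGT in a standard design".

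Section 2.7 names two between-group safety analyses. For counts, "A comparison of the number of AEs related with the trial will be conducted using the Kruskal–Wallis test". For incidence, "group comparisons of the proportion of subjects who experienced one or more AEs will be analyzed using Pearson's" chi-square or Fisher's exact test. The general rule is "All analyses will be set at a 5% significance level". The section attaches no effect estimate, confidence interval or tolerable excess to either comparison.

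Section 2.2.2 derives the sample size from TNSS only and concludes that "a total of 105 subjects (35 subjects per group) will be required". It gives no expected AE incidence and no power or precision for safety.

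**The concern.** A test of no difference answers a question about efficacy better than one about safety. When the hope is that the arms are alike, the favourable outcome of such a test is a large p-value. In a small trial a large p-value can arise because the arms are alike or because the test could not tell them apart. An estimate with an interval separates the two; a p-value alone does not.

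The trial also has to inform a choice between a standard dose and a dose twice as large. For that, the useful quantity is the excess AE incidence of each dose over placebo. Kruskal–Wallis across three groups does not supply it, and a chi-square or Fisher p-value does not either. If the report says only that AEs did not differ significantly, a reader cannot tell how large an excess the data leave open.

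**Working it through.** **Inputs.** From the article: 35 randomised per group and 1:1:1 allocation (2.2.2); 5% level (2.7), taken as two-sided because no side is stated; and a safety set defined by exposure: "Safety evaluation will be conducted in the subjects who took one or more interventions". That set should therefore be close to 35 per group, not the 29 left after dropout. Assumed, because the article gives none: placebo AE incidence of 5% to 30%.

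**1. The plan's own figure.** For a TNSS difference of 0.97, SD 1.3, 80% power and two-sided 5%:

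n = 2 × (1.96 + 0.84)² × (1.3 / 0.97)² ≈ 28.2, rounded up to 29 per group, as stated. The 35 equals 29 × 1.2 = 34.8, rounded up. The figure reproduces, and nothing in it refers to AEs.

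**2. Chance of missing a doubling on both doses, three-group Pearson test.** Statistic: Σ(xᵢ − n·p̄)² / [n·p̄(1 − p̄)], where xᵢ is the number with at least one AE in group i, n = 35 and p̄ is the pooled proportion. It is compared with the 5% point of chi-square on 2 df, and power is summed exactly over all 36³ outcomes.

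| Placebo / standard / high | Power | Missed |
|---|---|---|
| 5 / 10 / 10% | 9% | 91% |
| 10 / 20 / 20% | 20% | 80% |
| 15 / 30 / 30% | 30% | 70% |
| 20 / 40 / 40% | 45% | 55% |
| 25 / 50 / 50% | 60% | 40% |
| 30 / 60 / 60% | 76% | 24% |

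The exact (Fisher–Freeman–Halton) version is similar: 82% missed at 10 / 20 / 20%. If only one active arm doubles, Pearson misses 90% at a 5% placebo rate, 77% at 10%, 52% at 20% and 24% at 30%.

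**3. If the proportion tests are pairwise.** For 10% against 20% with 35 per group, the miss rate is 78% with Pearson and 87% with Fisher.

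**4. Kruskal–Wallis on counts.** With Poisson counts of mean 0.1 / 0.2 / 0.2 (an assumption), simulated power is 16%, so a doubling is missed about 84% of the time.

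**5. What an interval would show.** Take 8/35 on one dose and 3/35 on placebo as an illustration. Fisher's p is 0.19. The difference is 22.9% − 8.6% = 14.3 percentage points, with a Newcombe 95% CI of −3 to +31 points. The test reports no significant difference; the interval shows that an excess of up to about 31 points is not excluded.

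**6. Expected precision.** The Wald 95% half-width with equal true rates is 1.96 × √[2p(1 − p)/35]. At p = 10%: 1.96 × √(0.18/35) = 14 points. At p = 20%: 1.96 × √(0.32/35) = 19 points.

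**The case against.** The strongest objection is that this is a condensed article. Risk differences and intervals for AEs are commonly left to the full protocol or analysis plan, so their absence here is not in itself a fault. That stands. A reader might infer that the whole safety evaluation consists of these tests. The article does not support that: it shows only which between-group analyses it names, and 2.4.3 adds laboratory tests, vital signs, AE checks at every visit and reporting of serious AEs.

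Second, the named tests are valid for a three-arm trial, and sizing a phase II trial on its primary outcome is ordinary. This also stands. A reader might infer that the plan treats p > 0.05 as proof of safety, or will choose a dose on an AE p-value. No passage says either; the Discussion sentence is a general expectation and not a decision rule.

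Third, a reader might conclude that a doubling would be missed about 80% of the time whatever the circumstances. That figure holds only near a 10% placebo rate. At 25% or more, the three-group Pearson test would more often detect a doubling than miss it.

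Fourth, the proportion tests are not certainly three-group tests, since the wording leaves pairwise comparison open. Only Kruskal–Wallis is clearly a three-group comparison. Step 3 shows that the pairwise reading does not remove the problem at low rates.

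What survives is narrower: the article does state a method for the AE comparison, and that method does not yield the quantity its safety and dose aims call for.

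**Conclusion.** The point holds as a minor improvement, not as an error. The named AE comparisons are difference tests, not sized for safety, and they return no estimate or bound for either dose against placebo. At 35 per group a non-significant result is weak evidence of safety unless AEs are common: a doubling on both doses is missed more often than not at each placebo rate examined up to 20%, and about a quarter of the time at 30%.

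These sizes rest on assumed AE rates, a two-sided 5% level, 35 evaluable subjects per group and, for the main table, a three-group Pearson test. The need for an interval does not depend on the exact rate, because a p-value does not show how large an excess remains possible.

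**What to change.** In 2.7, state that for each dose against placebo the difference in the proportion of subjects with at least one AE will be reported with a 95% CI, for example by Newcombe's method. Keep the Kruskal–Wallis and chi-square or Fisher results as descriptive. State that the safety conclusion will rest on the interval and not on non-significance, and word the Discussion sentence on safety to match. If the full protocol or analysis plan already specifies such intervals, a one-line mention in 2.7 is enough.

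The cost is a few sentences and a few lines of code, with no extra patients, visits or data. The downside is a less favourable safety statement, because the wide intervals shown in step 6 will be on view.
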